#### Secondary endpoints

The following outcomes on the two treatment arms will be compared:HbA1c at 12 weeksTime spent below target glucose (3.9 mmol/L) (70 mg/dL)Time spent above target glucose (10.0 mmol/L) (180 mg/dL)Average, SD and coefficient of variation of glucose levelsTime with glucose levels <3.5 mmol/L (63 mg/dL) and <2.8 mmol/L (50 mg/dL)Time with glucose levels in the significant hyperglycaemia (glucose levels >16.7 mmol/L) (300 mg/dL)Total, basal and bolus insulin dose (units/kg of body weight)Area under the curve of glucose below 3.5 mmol/L (63 mg/dL)Number of pump suspend events (applicable to intervention arm)Change in body weight from screening to end of study.

Glycaemic metrics will be based on sensor glucose levels collected during the 12-week intervention period. Similar linear models as the primary outcome will be used to compare the between-treatment difference. For those metrics that have highly skewed distribution, a ranked normal score transformation of outcome data will be applied in the regression model. p Value <0.05 will be used to declare statistical significance for selected secondary outcomes (HbA1c, glucose CV, % time below 3.9 mmol/L, % time above 10.0 mmol/L, total daily insulin and change in body weight). For other outcomes, to reduce the inflation of type I error caused by multiple comparisons, p value <0.01 will be used to define statistical significance.

A subset of sensor glucose and insulin metrics will also be tabulated separately for daytime period (08:00–00:00) and night-time period (00:00–08:00).Percent time with glucose in target range of 3.9–10.0 mmol/L (70–180 mg/dL)Mean glucoseGlucose variability as measured by SDPercent time with glucose level <3.5 mmol/L (63 mg/dL)Amount of delivered insulin.

Trends in sensor glucose data collected within intervention arms will be evaluated on a 4-weekly basis.

### Safety analysis

The following safety outcomes will be tabulated by treatment group:Number of subjects with any DKA eventsNumber of episodes of DKA events per subject and incidence rate per 100 person-yearsNumber of subjects with any severe hypoglycaemia eventsNumber of episodes of severe hypoglycaemia events per subject and incidence rate per 100 person-yearsNumber of subjects with any severe hyperglycaemia events as defined by fingerprick glucose >16.7 mmol/L (>300 mg/dL) and plasma ketones >0.6 mmol/LNumber of episodes of severe hyperglycaemia events per subject and incidence rate per 100-person years.

Above safety data will be tabulated for all subjects in the two intervention periods, including dropouts and withdrawals, irrespective of whether sensor glucose data are available and irrespective of whether closed loop was operational. All adverse events will be listed for the entire study duration.

If there are enough observed events to allow formal statistical modelling for above safety outcomes, the following analyses will be conducted. The event rates will be compared using a Poisson regression model adjusting for random site effect. If outliers exist, a robust Poisson regression model will be used instead. Binary variables will be compared using a logistic regression model adjusting for random site effect. Models involving severe hypoglycaemia events will also adjust for severe hypoglycaemia in the previous 6 months before enrolment.

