### Exclusion criteria

Non-T1D including those secondary to chronic diseaseUsing real-time CGM on regular basis in preceding 3 monthsAny other physical or psychological disease likely to interfere with the normal conduct of the study and interpretation of the study results as judged by the investigatorUntreated coeliac disease, adrenal insufficiency or hypothyroidismCurrent treatment with drugs known to interfere with glucose metabolism, for example, systemic corticosteroids, non-selective beta-blockers and monoamine oxidase inhibitors, among othersKnown or suspected allergy to insulinClinically significant nephropathy (estimated glomerular filtration rate <45 mL/min) or on dialysis, neuropathy or active retinopathy (defined as the presence of maculopathy or proliferative changes) as judged by the investigatorAdults: one or more episodes of severe hypoglycaemia as defined by American Diabetes Association^19^ in preceding 6 months; youths: one or more episodes of severe hypoglycaemia during the previous 6 months (adults and adolescents: severe hypoglycaemia is defined as an event requiring assistance of another person to actively administer carbohydrates or glucagon or take other corrective actions including episodes of hypoglycaemia severe enough to cause unconsciousness, seizures or attendance at hospital; children: severe hypoglycaemia is defined as an event associated with a seizure or loss of consciousness)Random C peptide >100 pmol/L with concomitant blood glucose >4 mmol/L (72 mg/dL)Regular use of acetaminophenLack of reliable telephone facility for contactTotal daily insulin dose ≥2 IU/kg/dayTotal daily insulin dose <15 IU/dayPregnancy, planned pregnancy or breast feedingSevere visual impairmentSevere hearing impairmentSignificantly reduced hypoglycaemia awareness in participants aged 18 years and older defined by Gold score of >4Using implanted internal pace-makerMedically documented allergy towards the adhesive (glue) of plasters or unable to tolerate tape adhesive in the area of sensor placementSerious skin diseases (eg, psoriasis vulgaris, bacterial skin diseases) located at places of the body, which potentially are possible to be used for the localisation of glucose sensorCurrently abusing alcohol, illicit drugs or prescription drugsUsing pramlintide (symlin) or other commonly used hypoglycaemic agents including sulphonylureas, biguanides, DPP4 inhibitors, GLP-1 agonists, SGLT-2 inhibitors at time of screeningElective surgery planned that requires general anaesthesia during the course of the studyShift worker with working hours between 22:00 and 08:00Sickle cell disease or haemoglobinopathyRed blood cell transfusion or erythropoietin within 3 months prior to the time of screening or plans to receive red blood cell transfusion or erythropoiesstin during the course of study participationDiagnosed with current eating disorder such as anorexia or bulimiaPlans to use significant quantity of herbal preparations (use of over-the-counter herbal preparation for 30 consecutive days or longer period during the study) or significant quantity of vitamin supplements (four times the recommended daily allowance used for 30 consecutive days or longer period during the study), which may affect glucose metabolism and/or blood glucose levels during the course of their participation in the study.

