#### Primary endpoint

The primary analysis will evaluate between group difference in the time (midnight to midnight) spent in the target glucose range from 3.9 to 10.0 mmol/L (70–180 mg/dL) based on sensor glucose levels during the 12-week free-living phase.

A 5% significance level will be used to declare statistical significance for the primary outcome comparison.

Mean (SD) for % time spent in the target range will be tabulated by treatment group. A linear model will be used to compare the difference between the two intervention arms, while adjusting for baseline % time spent in the target glucose range and random site effect. A 95% CI will be reported for the difference between the treatment groups based on the linear model. Normality of the residuals will be assessed. If the residuals have highly skewed distribution, then ranked normal score transformation of outcome data will be applied in the regression model. However, previous experience suggests that % time in target glucose range will follow an approximately normal distribution. A detailed analysis plan will be provided separately.

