### Power calculation

On the basis of our previous day-and-night closed-loop studies^10 23^ and a conservative estimate of 10%points improvement in time when glucose is in target glucose range with an SD of 14.5% points, 76 subjects are required to achieve 85% power and an alpha level of 0.05 (two tailed). A total of 84 are planned to be randomised to allow for dropouts. It is expected that 95 or more subjects will be recruited; recruitment will continue until it is anticipated that a sufficient number have been enrolled to meet the randomisation goal. Randomisation target may be exceeded since all of the subjects who have initiated the run-in phase will be permitted to continue into the intervention.

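### Recurrent safety event rates default to plain Poisson regression, and the robust model is tied to outliers instead of to clustering of episodes within a person

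*Protocol article*

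**What the plan says.** The Safety analysis section of the protocol article lists, for each of three event types, the number of subjects with any event, the number of episodes per subject, and a rate per 100 person-years. Repeat episodes in one person therefore count towards the rate.

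Formal comparison is conditional: "If there are enough observed events to allow formal statistical modelling for above safety outcomes, the following analyses will be conducted". For rates, the default is: "The event rates will be compared using a Poisson regression model adjusting for random site effect". The one stated departure from it is: "If outliers exist, a robust Poisson regression model will be used instead". For subjects with any event: "Binary variables will be compared using a logistic regression model adjusting for random site effect".

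One person-level covariate is named: "Models involving severe hypoglycaemia events will also adjust for severe hypoglycaemia in the previous 6 months before enrolment". The Exclusion criteria, however, rule out people with "one or more episodes of severe hypoglycaemia during the previous 6 months".

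**The concern.** Poisson regression sets the variance of a count equal to its mean. If some participants are more prone to episodes than others, the variance exceeds the mean and the Poisson standard error is too small. A random site effect absorbs differences between sites, not between people at the same site. The previous-6-months covariate can do little, because the exclusion criterion makes it almost constant, and it enters only the hypoglycaemia models.

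The switch to a robust model does not close the gap, because its trigger looks for the wrong thing. Counts can be overdispersed when many participants have none, several have two or three, and nobody stands out. How an outlier is defined could be left to a separate analysis plan. But the article already fixes the default and the type of trigger, and no definition of an outlier turns it into a check for overdispersion.

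At stake are over-precise intervals and too many chance findings in the between-arm comparison of event rates.

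**Working it through.** **Inputs from the documents.** The Power calculation section says: "A total of 84 are planned to be randomised to allow for dropouts". I take this as 42 per arm (1:1 allocation is assumed). The intervention lasts 12 weeks, so each arm has about 42 × 84/365.25 = 9.7 person-years.

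**The plan's own figure.** The safety models have none. The only design figure concerns the primary endpoint, and it reproduces: 2 × (1.960 + 1.036)² × 14.5²/10² = 37.8, so 38 per arm and 76 in all, with power 85.2% (84.3% by noncentral t).

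**Assumptions.** The documents give no event rate and no dispersion. Let mu be the mean number of episodes per person over 12 weeks and k the dispersion, with variance mu(1 + k·mu). Means of 0.2, 0.5 and 1 correspond to about 87, 217 and 435 events per 100 person-years.

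**Standard error.** The Poisson standard error is 1/sqrt(1 + k·mu) of the correct one. The approximate type I error of a nominal 5% test is 2 × [1 − Φ(1.96/sqrt(1 + k·mu))].

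| 1 + k·mu | Standard error too small by | Type I error |
|---|---|---|
| 1.5 | 18% | 11% |
| 2 | 29% | 17% |
| 3 | 42% | 26% |

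**Simulation with no true difference.** Gamma-Poisson counts, 42 per arm, Wald test on the log rate ratio, 100,000 trials per setting. The site effect is left out because it does not model repeat events within a person.

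| Mean per person | k | Plain Poisson | Always sandwich |
|---|---|---|---|
| 0.2 | 1–4 | 5.8–11.4% | 4.9–6.2% |
| 0.5 | 1–4 | 10.1–24.5% | 5.8–7.7% |
| 1 | 1–4 | 16.1–37.3% | 6.1–7.9% |

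With k = 0, plain Poisson is valid: 4.6% at a mean of 0.5 and 4.8% at a mean of 1. At a mean of 0.1 (about 4 events per arm) it stays below 5% even at k = 4 (3.4%). That last result is specific to the Wald test. A likelihood-ratio test at the same mean gave 5.3% at k = 0 and 9.3% at k = 4, but so few events may well not be modelled at all.

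**The plan with its switch.** Here robust is read as sandwich variance, and an outlier is assumed when the highest count has a Poisson tail probability below 0.001 (20,000 trials per setting).

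| Mean, k | Plain Poisson | With the switch | Always sandwich |
|---|---|---|---|
| 0.2, 2 | 7.6% | 6.1% | 5.2% |
| 0.5, 1 | 10.0% | 7.8% | 5.8% |
| 0.5, 4 | 24.5% | 8.3% | 7.6% |
| 1, 2 | 25.5% | 7.5% | 6.8% |
| 1, 4 | 36.5% | 8.0% | 7.9% |

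A stricter trigger of 0.0001 raises the upper end to about 11%. Over both triggers the range is about 5–11%.

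**Can an outlier check miss the problem?** At a mean of 0.5 and k = 2, no participant had more than 4 events in 42% of simulated trials. Among those trials plain Poisson still rejected 11% of the time.

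**The case against.** **The plan is not plain Poisson throughout.** A reader might infer from the first simulation that the plan carries a false-positive rate of up to 37%. The documents do not support that. The settings with the largest inflation are those that produce conspicuous high counts: at a mean of 1 and k = 4 the assumed 0.001 rule fires in 99% of trials. Under that rule the excess over an always-sandwich analysis is about 0–2 percentage points, and up to about 5 under the stricter one. This stands, and it sets the size of the point.

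**The scope is narrow.** The withdrawal criteria remove a participant after one severe hypoglycaemia related to closed loop, after three unrelated ones, or after certain closed-loop-related ketoacidosis. These rules limit repeats of two of the three event types. No event-count rule limits severe hyperglycaemia with ketones, which is the outcome mainly exposed. This also stands.

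**The models run only if events are numerous enough.** True, but this gate offers limited protection. It tends to leave out sparse data, where the Wald error is small, and to admit frequent events, where clustering matters.

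**Suppressed signal.** A reader might infer that a robust model would down-weight the participants with most events and hide a safety signal. That is only one possible meaning of robust, and the article does not say it is the one intended. Episodes and rates are tabulated by arm whatever the model, and the any-event comparison is separate, so such participants stay visible.

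**A separate analysis plan is announced.** It may define outlier and robust, and their absence from a condensed article is no fault. What remains is the default and trigger that the article does fix.

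**Conclusion.** The point holds as a minor one. The stated default does not account for clustering of episodes within a person, and outliers are the wrong trigger for correcting it. Moderate overdispersion without an extreme participant would go through with standard errors that are too small, mainly for severe hyperglycaemia with ketones.

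The fair comparison is about 5–11% type I error for the plan with its switch against 5–8% for a sandwich variance used throughout. The 6–37% range describes plain Poisson only and is not the plan's error rate. All these figures rest on assumed means of 0.2–1, k of 1–4 and 42 per arm; the first range also rests on the assumed outlier rule and on reading robust as sandwich variance. If episodes do not cluster, nothing is wrong with the default. The primary endpoint and the logistic analyses of any event are untouched.

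**What to change.** In the Safety analysis section, and in the analysis plan, name one prespecified model for all recurrent event rates: Poisson regression with a person-level sandwich variance, or negative binomial regression. Delete the sentence that makes the robust model conditional on outliers. The gate on having enough events and the logistic analyses can stay as they are.

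This is a change of wording, with no new data and no effect on sample size. The downside is wider intervals when episodes do cluster. When they do not, the sandwich costs almost nothing: its type I error was 5.3–5.4% at k = 0 with means of 0.5–1. With 42 per arm it is still slightly liberal under strong clustering (up to about 8% at k = 4).

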### Utility evaluation

The amount of CGM use will be calculated for both intervention arms, and the amount of closed-loop system used will be calculated for the closed-loop treatment arm only over the 12-week intervention and by 4-weekly period. The difference in CGM use between treatment groups will be compared using similar linear model as described for primary outcome.

### Subgroup analysis

No subgroups were considered during the power calculations. Interpretation of any subgroup analyses will depend on whether the overall analysis demonstrates a significant treatment group difference. In the absence of such an overall difference and if performed, the following subgroup analyses will be interpreted with caution: (1) age (6–12 years, 13–21 years, 22 years and older), (2) gender, (3) race–ethnicity, (4) clinical centre and (5) baseline HbA1c (<8.5% and ≥8.5%).

### Psychosocial evaluation

Questionnaires for diabetes-related quality-of-life assessment (PedsQL v3.2) will be collected at screening and at the end of the study intervention. For subjects ≥18 years of age, only answers from the participants themselves will be collected; for subject s≤17 years of age, answers will be collected from both parent version and child version.

At each assessment time point, mean±SD score for each dimension and the total score will be tabulated by intervention arm for both parent version and participant version. The between-group difference of each score at end of study will be assessed using a similar linear model as described previously by adjusting for corresponding score at baseline.

Interview data will be analysed thematically and longitudinally using the method of constant comparison.^22^ To maximise rigour, at least two experienced qualitative researchers will be involved in the analysis. NVivo9, a qualitative software package, will be used to facilitate data coding/retrieval.

### Per-protocol analysis

Per-protocol analysis will be conducted to compare the primary endpoint limited to participants who used closed loop for at least 80% of the of the 3-month study period (with CGM data are available for at least 50% of the study period). In the SAP group, per-protocol analysis will be conducted on those whose CGM data are available for at least 50% of study period.

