### Run-in period

There will be a minimum 4-week run-in period. Participants will be contacted once weekly by phone or email for troubleshooting purposes. At the end of the run-in period, study devices will be downloaded to assess adherence during the last 14 days (participants will be required to demonstrate at least 12 days’ use of CGM and use of at least 75% of bolus calculator for meal boluses for randomisation). Participants need to perform weekly downloads of study devices.

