### Safety precautions during closed-loop

Participants will be trained to perform calibration checks before breakfast and evening meals. If sensor glucose is above finger-stick glucose by more than 3.0 mmol/L, the glucose sensor will be recalibrated. These instructions resulted from an in-silico simulation of hypoglycaemia and hyperglycaemia risk using the validated Cambridge simulator.^21^

If sensor glucose becomes unavailable, preprogrammed insulin delivery will be automatically started within 30 min. This limits the risk of insulin underdelivery and overdelivery. Safety rules limit maximum insulin infusion and suspend insulin delivery at sensor glucose at or less than 4.3 mmol/L or when sensor glucose is rapidly decreasing.

In the event of closed-loop becoming unavailable due to loss of sensor glucose input or other system failures, insulin delivery will be suspended by the low glucose suspend feature set on the insulin pump, provided sensor glucose is available. Resumption of insulin delivery will be in accordance of the low glucose suspend feature implemented on 640G pump.

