### Statistical analysis

All analysis will be conducted on an intention-to-treat basis. Data from all randomised participants with or without protocol violation including dropouts and withdrawals will be included in the analysis. Data will not be truncated due to protocol deviations.

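### The per-protocol set is cut at 80% closed-loop use in one arm and 50% CGM data in the other, and this unequal selection can favour closed loop

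*Protocol article*

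**What the plan says.** The section 'Per-protocol analysis' defines a different rule for each arm.

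- Closed-loop arm: "limited to participants who used closed loop for at least 80% of the of the 3-month study period", with the further condition in brackets "with CGM data are available for at least 50% of the study period".
- Control arm (sensor-augmented pump): "In the SAP group, per-protocol analysis will be conducted on those whose CGM data are available for at least 50% of study period". No other adherence condition is set for controls.

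Three other places bear on how these rules work.

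- 'Safety precautions during closed-loop': "If sensor glucose becomes unavailable, preprogrammed insulin delivery will be automatically started within 30 min".
- 'Run-in period': to be randomised, in either arm, "participants will be required to demonstrate at least 12 days’ use of CGM" within the last 14 days.
- 'Statistical analysis': "All analysis will be conducted on an intention-to-treat basis". The per-protocol comparison is given no decision role.

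**The concern.** Both rules use the study period as denominator, so they can be put on one scale. Closed loop cannot run for long without sensor glucose, so a participant with 80% closed-loop use has about 80% or more sensor use. The intervention arm is in effect held to about 80% sensor use and the control arm to 50%.

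Sensor use is observed after randomisation and may go with engagement and better glucose control. Keeping only the more persistent users in one arm, while keeping nearly everyone in the other, means that the two sets are no longer comparable. If use and time in target are positively related, the closed-loop mean is raised by selection alone. The comparison is of the primary endpoint, so readers will set it beside the intention-to-treat estimate and may take a larger per-protocol difference as evidence of efficacy in adherent users.

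**Working it through.** **1. The plan's own figure.** 'Power calculation' assumes "a conservative estimate of 10%points improvement in time when glucose is in target glucose range with an SD of 14.5% points", 85% power and two-sided 0.05. With 1:1 allocation (assumed), n per arm = 2 × (1.960 + 1.036)² × 14.5² / 10² = 37.8, so 38 per arm and 76 in total. This reproduces the stated 76. The SD of 14.5 and the design effect of 10 are used below as the scale.

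**2. The two cut-offs on one scale.** Closed-loop arm: closed-loop use of at least 80%, hence sensor use of about 80% or more. Control arm: CGM data of at least 50%. For comparison, the run-in screen is 12/14 = 86% of days. Days of use are not percent of time, and use may fall later, but 50% is a low bar for people who have passed that screen.

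**3. Size with no treatment effect.** Suppose sensor use is normal with the same mean and SD in both arms and correlates r with time in target (SD 14.5). Selecting those above a cut-off c shifts the mean outcome by r × 14.5 × λ(c), where λ(c) = φ(z)/(1 − Φ(z)) and z = (c − mean)/SD. The spurious difference is

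r × 14.5 × [λ(80) − λ(50)].

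This takes closed-loop use as equal to sensor use. The mean, SD and r are assumptions; the protocol gives none of them.

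| Mean, SD of use (%) | λ(80) | λ(50) | Closed loop kept | Controls kept | r = 0.2 | r = 0.3 | r = 0.4 |
|---|---|---|---|---|---|---|---|
| 75, 12 | 1.081 | 0.046 | 34% | 98% | 3.0 | 4.5 | 6.0 |
| 80, 12 | 0.798 | 0.018 | 50% | 99% | 2.3 | 3.4 | 4.5 |
| 85, 10 | 0.509 | 0.001 | 69% | about 100% | 1.5 | 2.2 | 2.9 |
| 90, 8 | 0.204 | 0.000 | 89% | about 100% | 0.6 | 0.9 | 1.2 |

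Worked row (80, 12, r = 0.3): 0.3 × 14.5 × (0.798 − 0.018) = 3.4 points. At r = 0 every entry is 0.

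**4. Cross-check by retention.** Keeping a top fraction k shifts use by φ(z)/k SDs, with z the cut point for k. With 95% of controls kept the shift is 0.109. If 50% of the closed-loop arm qualifies, the difference is r × 14.5 × (0.798 − 0.109), that is 1.0 to 5.0 points for r = 0.1 to 0.5. If 90% qualifies, it is r × 14.5 × (0.195 − 0.109), that is 0.1 to 0.6 points. The size depends mainly on how many closed-loop participants fall below 80%.

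**5. What a common threshold achieves.** With the same cut-off on the same measure in both arms, the two shifts cancel and the difference in this illustration is 0. Keeping the extra closed-loop condition in one arm brings some of it back. Assume closed-loop time is 95% of sensor time for everyone: 80% closed-loop use then needs 80/0.95 = 84.2% sensor use. At mean 80, SD 12, λ(84.2) = 1.034. The residual at r = 0.3 is 0.3 × 14.5 × (1.034 − 0.798) = 1.0 point, against 0.3 × 14.5 × (1.034 − 0.018) = 4.4 under the stated rule. At a ratio of 90% the cut-off is 88.9%, λ = 1.322, and the figures are 2.3 and 5.7. The fix reduces the selection difference but does not remove it.

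**The case against.** The strongest case against the point has five parts.

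- **Direction and size are assumed.** A reader might infer that the analysis will show a closed-loop benefit when there is none. The documents do not support that. It needs a positive correlation between use and time in target, on which the protocol has no figure. This stands: the rule *can* favour closed loop, no more.
- **Use may be high.** Given the run-in screen, mean use near 90% is plausible, and the spurious difference is then only 0.6 to 1.2 points. This stands, and the range has to include it. For the same reason, the view that nearly all controls qualify is an inference from the run-in rule, not a stated figure.
- **Baseline adjustment.** The primary model adjusts for baseline time in target. If the per-protocol comparison uses it, any association carried by baseline control is at least partly removed. This stands: the table is before adjustment. Adjustment does not remove differences in engagement that arise after randomisation.
- **The 50% clause in the closed-loop arm may do some work.** It concerns available data, and pump downloads ('Devices download') are separate from the phone's upload ('Closed-loop system and low glucose suspend feature'). It could act as a floor when downloads are lost. This stands: the clause is practically redundant for sensor wear, not shown to be empty.
- **Some asymmetry cannot be avoided.** Closed-loop use has no counterpart in the control arm. True, but CGM use can be measured in the same way in both arms, so this does not justify two different sensor-use cut-offs.

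**Conclusion.** The point holds as a flaw in how the per-protocol set is defined. The rule selects the arms at effective sensor-use cut-offs of about 80% and 50% after randomisation. With no treatment effect it can produce a difference in favour of closed loop of roughly 0.6 to 6 points, for mean use of 75–90%, SD 8–12% and r = 0.2–0.4, before baseline adjustment and with closed-loop use taken as equal to sensor use. It is near zero if the correlation is near zero. All of these inputs except the SD of 14.5 are assumptions.

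A reader might go further and infer that the trial's main conclusion is biased, or that the protocol relies on this analysis to confirm it. Neither follows. The primary analysis is by intention to treat, the sample size is unaffected, and the protocol does not present the per-protocol comparison as a robustness check. What is at stake is how a planned secondary comparison of the primary endpoint will be read.

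**What to change.** In 'Per-protocol analysis', and in the separate analysis plan:

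1. Set one CGM-use threshold for both arms, measured in the same way over the same period. At least 80% is an example that matches the existing closed-loop cut-off; the documents give no other basis for a value.
2. Keep the closed-loop-use condition as an addition in the intervention arm. The 50% CGM clause there can then go, since the common threshold covers it.
3. State that the result is supportive only, because the added closed-loop condition has no control counterpart and leaves some residual selection in favour of closed loop.

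The change is one of wording. Its cost is a smaller control per-protocol set: under the assumed distributions, an 80% cut-off would keep 34–89% of controls instead of 98–100%, with a matching loss of precision in a comparison that carries no formal decision.
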